**Methods:**

To investigate the efficacy of CFT compared with a sham intervention for pain intensity and disability post-intervention (immediately after the last session) in patients with non-specific chronic low back pain (CLBP). This study is a randomized controlled trial in which 152 (18–60 years old) patients with CLBP will be enrolled. The patients will be randomly allocated to receive (1) CFT intervention or (2) sham intervention. The experimental group will receive individualized CFT in a pragmatic manner (5 to 7 sessions) based on the clinical progression of the participants. The sham group will attend six sessions: consisting of 30 min of photobiomodulation using a detuned device and more than 15 min of talking about neutral topics. Patients from both groups also will receive an educational booklet (for ethical reasons). Participants will be assessed pre and post-intervention, 3 months, and 6 months after randomization. The primary outcomes will be pain intensity and disability post-intervention. The secondary outcomes will be: pain intensity and disability at 3- and 6-month follow-up, as well as self-efficacy, global perceived effect of improvement, and functioning post-intervention, 3-, and 6-month follow-up. The patients and the assessor will be blinded to the treatment administered (active vs. sham).

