### Procedures, randomization, and allocation

The study will follow the recommendations described on Consolidated Standards of Reporting Trials (CONSORT) statement [29], the current report followed the Standard Protocol Items: Recommendations for Interventional Trials (SPIRIT) document [30], and the Template for Intervention Description and Replication (TIDieR) checklist for placebo and sham controls [31]. The description of interventions as recommended by TIDieR can be found in supplementary material 1.

Patients will be informed that this study will involve a sham intervention arm (fake intervention in which an inert treatment will be provided but it still can result in positive outcomes due to its psychological effects) vs. an active treatment arm, but the nature of the sham will not be elucidated (equipment detuned). After this initial assessment, participants will be randomly assigned using block randomization by simple computerized procedures to one of the two treatment groups through the use of cards previously placed in opaque sealed envelopes: (i) CFT group or (ii) sham group. The allocation sequence will be generated by a researcher not involved in the assessment and interventions ([name]), and another research assistant will assign participants to interventions (Fig. 1). Each participant will be treated by a single physiotherapist, who will not be involved in the assessment of the patients. Participants will not have knowledge about treatment allocation. One blinded researcher regarding treatment group allocation will run the assessments pre-treatment, immediately after, and at the follow-ups.

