### Outcome measures

The primary outcomes in the current study will be pain intensity [32] and low back pain-related disability [27] collected post-intervention. The secondary outcomes will be pain intensity and low back pain-related disability at 3 and 6 months after randomization, as well as self-efficacy [33], global perceived effect of improvement [32], and functioning [32] post-intervention, 3, and 6 months after randomization. In the baseline, we will administer scales to assess moderating effect: expectation [34], depression [35], anxiety [36], kinesiofobia [37], and pain catastrophizing [38]. Mini-Mental State Examination (MMSE) [39] will be administered to assess the cognitive function of the volunteers. Patients with a score lower than 24 will be excluded [40]. The questionnaires will be administered in an assisted interview mode.

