### Statistical analysis

All randomized patients will be analyzed on an intention-to-treat basis. Baseline characteristics will be presented by the treatment group. Binary and categorical variables will be summarized by frequencies and percentages. The between-group differences (effects of treatment) and their respective 95% CIs will be calculated by constructing linear mixed models. Treatment effect for the primary and continuous secondary outcomes will be estimated using mixed linear models, considering the correlation within the individual. The mixed linear model will include random intercept adjusted with the baseline score, time as categorical, and the interaction between treatment and time. We will use strategies to reduce the attrition rate during follow-ups as telephone calls and an active search of information.

Two primary outcome variables were considered for the calculation of sample size. For pain intensity, an improvement of at least 1-point on the NPRS (SD=1) and a mean difference of at least 5 points for the ODI score (SD=10). The following specifications were considered: α=5%, 80% statistical power, effect size of 0.27 for *F*-test, and a follow-up attrition rate of 15%. The final sample size will be comprised of 152 patients (76 per group) (G*Power©, University of Dusseldorf, Germany). A moderator effect of baseline variables including the expectation to treatment will be calculated using regression analysis and structural equation modeling (*path analysis*) (AMOS (SPSS, v.22). Data will be coded and entered into the Statistical Package for the Social Sciences (SPSS), version 22 (Chicago, IL, IBM corp., USA) program for analysis and the significance level will be established at 0.05. The Bonferroni correction will be used to adjust the *p*-values for multiple primary outcomes [47]. The data collected will be stored and coded to protect patient confidentiality. In order to handle missing data, we will replace the value with the last observation carried forward. The researchers involved in the study will have access to the final trial dataset and, upon request, it can be shared for the purposes of results conference and publication. The results of the study will be disseminated to interested parties through publications in an appropriate journal.

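### The planned mixed model is valid, but one baseline slope for all visits and own-baseline adjustment only leave a little precision unused at the primary visit

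*Protocol article*

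**What the plan says.** The article's Statistical analysis section lists the terms of the efficacy model: "The mixed linear model will include random intercept adjusted with the baseline score, time as categorical, and the interaction between treatment and time". It names no baseline-by-time term and no covariate other than the outcome's own baseline.

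The abstract gives the visits: "Participants will be assessed pre and post-intervention, 3 months, and 6 months after randomization". The model therefore covers three post-baseline visits. Outcome measures makes one of them decisive: "The primary outcomes in the current study will be pain intensity [32] and low back pain-related disability [27] collected post-intervention".

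Five psychological measures are also taken at baseline and given a moderator role ("In the baseline, we will administer scales to assess moderating effect"). Their analysis is described apart from the efficacy model: "A moderator effect of baseline variables including the expectation to treatment will be calculated using regression analysis". Allocation is by "block randomization by simple computerized procedures", with no stratification factor stated, so the model omits none.

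**The concern.** A single baseline slope is a compromise between three visits. If the outcome's correlation with baseline is higher at post-intervention than at 3 and 6 months, the slope applied at the primary visit is too shallow for it, and some explainable variance stays in the standard error. Each primary outcome's baseline may also help to predict the other outcome, and both are collected anyway.

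What is at stake is precision on ODI. Under the plan's own inputs ODI is the harder primary outcome: 5 points with SD 10 is d = 0.5, against d = 1.0 for NPRS. The trial was sized at "α=5%, 80% statistical power", while the two primary outcomes are to be Bonferroni-corrected. At 0.025, ODI therefore relies on covariate adjustment to reach 80% power.

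**Working it through.** **Inputs from the article:** ODI difference 5, SD 10; alpha 0.05; power 80%; attrition 15%; 152 patients (76 per group); Bonferroni over two primary outcomes, so 0.05/2 = 0.025 each.

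**Assumed, because the article does not give them:** correlations of the outcome with its baseline at the three visits (r1, r2, r3), partial R² of further covariates, two-sided testing, equal variances across visits, and complete data on 64 patients per arm.

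**1. The plan's own figure.** d = 5/10 = 0.5, so f = 0.25. The noncentral F calculation at alpha 0.05 and 80% power gives 128, or 64 per arm. Then 64/0.85 = 75.3, rounded up to 76, gives 152, which matches. (The printed effect size of 0.27 would give 110, or 130 after attrition; that is a separate matter.) Unadjusted ODI power with 64 per arm is 0.801 at 0.05 and 0.712 at 0.025.

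**2. Cost of the shared slope.** With complete data and a random intercept, the shared slope is b = (r1 + r2 + r3)/3, in units where the SD is 1. The post-intervention contrast is the raw difference minus b times the baseline difference. Its residual variance is

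- shared slope: V = 1 − 2·b·r1 + b²
- visit-specific slope: V = 1 − r1²

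| r1 / r2 / r3 | b | V shared | V specific | Variance ratio |
|---|---|---|---|---|
| 0.5 / 0.5 / 0.5 | 0.500 | 0.750 | 0.750 | 1.000 |
| 0.6 / 0.55 / 0.5 | 0.550 | 0.6425 | 0.640 | 1.004 |
| 0.6 / 0.5 / 0.4 | 0.500 | 0.650 | 0.640 | 1.016 |
| 0.6 / 0.45 / 0.3 | 0.450 | 0.6625 | 0.640 | 1.035 |
| 0.5 / 0.3 / 0.2 | 0.333 | 0.778 | 0.750 | 1.037 |
| 0.6 / 0.4 / 0.2 | 0.400 | 0.680 | 0.640 | 1.063 |
| 0.7 / 0.5 / 0.3 | 0.500 | 0.550 | 0.510 | 1.078 |

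Modest declines cost 0% to about 4% of the variance (under 2% of the SE). Steep declines cost about 6% to 8%. A still more extreme 0.7/0.4/0.2 would give 14%.

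**3. Simulation check** (3,000 trials, 76 per arm, complete data). The SE of the post-intervention contrast in SD units, shared against visit-specific, was 0.1405 and 0.1406 at 0.5/0.5/0.5, 0.1320 and 0.1313 at 0.6/0.5/0.4, and 0.1329 and 0.1305 at 0.6/0.4/0.2. Unadjusted it was about 0.16. With no true effect, the adjusted estimates averaged within 0.006 of zero.

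**4. ODI power at 0.025 with 64 per arm.** Noncentral t on 126 df, with noncentrality (0.5/√V)·√(64/2). Further covariates multiply V by (1 − partial R²).

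| r1 / r2 / r3 | Planned model | Visit-specific slope | Also partial R² 0.05 | Also partial R² 0.10 |
|---|---|---|---|---|
| 0.5 / 0.5 / 0.5 | 0.839 | 0.839 | 0.859 | 0.878 |
| 0.5 / 0.3 / 0.2 | 0.825 | 0.839 | 0.859 | 0.878 |
| 0.6 / 0.45 / 0.3 | 0.885 | 0.896 | 0.911 | 0.926 |

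The whole change adds about 2 to 5 points, of which the slope term supplies 0 to about 1.5. Going from unadjusted (0.712) to the planned model adds 11 to 17 points, so own-baseline adjustment already captures most of the gain.

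**The case against.** The strongest objection is that nothing here is wrong. A baseline-adjusted mixed model with categorical time and treatment-by-time is valid under randomization, and preferring a richer covariate set is optimization. That stands. A reader might infer that the primary contrast is biased or the trial under-adjusted; the article does not support either. If correlations were 0.6/0.45/0.3, a 2-SE baseline ODI imbalance (2 × 10 × √(2/76) = 3.2 points) would leave 3.2 × (0.60 − 0.45) ≈ 0.5 points uncorrected. That is a conditional error in an unusual trial, with three quarters of the imbalance effect removed (0.45/0.60). It is not a systematic bias.

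A reader might also expect power to rise from 80% to 82–84%. That applies the extra covariates to an unadjusted analysis at 0.05. The planned model already adjusts for own baseline: at 0.6/0.45/0.3 its power is about 93% at 0.05 and 88.5% at 0.025.

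The article is condensed, its sentence does not name a treatment main effect either, and a full analysis plan may add terms. This too stands in part: the point rests on the terms as listed.

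Finally, the correlations may differ little. Five to seven weekly sessions put post-intervention only some 6 to 8 weeks before the 3-month visit, and carrying the last observation forward tends to make visits more alike. Both push the slope loss toward zero. They do not affect the gain from the other outcome's baseline.

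It would also go too far to say that the psychological scales are barred from the efficacy model. The article gives them a moderator role and does not call it exclusive.

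**Conclusion.** The point holds as a low-severity efficiency suggestion. It identifies no error, contradiction or wrong figure in the article. As listed, the model gives up 0% to about 4% of the variance of the post-intervention contrast, about 8% at 0.7/0.5/0.3, and nothing when correlations are equal. With the other outcome's baseline added, ODI power at 0.025 rises by roughly 2 to 5 points over the planned model, provided the partial R² is 0.05 to 0.10; a weaker covariate would bring less. These sizes rest on assumed correlations and partial R², equal variances and complete data, and none can be derived from the article. The gain is worth having mainly for ODI, because unadjusted ODI power at the Bonferroni level is only about 0.71. The mismatch between sizing at 0.05 and testing at 0.025 is a separate and larger issue.

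**What to change.** Before unblinding, state in the analysis plan that (a) the mixed models include a baseline-score-by-time interaction; (b) baseline NPRS and baseline ODI are both covariates in both primary models; and (c) the primary treatment effect is the post-intervention contrast from that model. Name the covariates outright and leave no optional ones. The psychological scales need not enter the efficacy model.

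The cost is a sentence or two of wording and about three degrees of freedom (two for the interaction, one for the second baseline) against about 128 completers. No new data are needed. Taking three degrees of freedom from 126 changes the power figures above by less than 0.001. If the second baseline predicted nothing, it would inflate the variance by about 1/123, or 0.8%.

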### Primary outcomes

#### Pain intensity

Numeric pain rating scale (NPRS) will be used to assess pain intensity. The NPRS used in this trial will consist of numbers from 0 to 10, in which 0 represents “no pain” and 10 represents “worst pain imaginable” [32]. NPRS showed responsiveness to change, with a minimum clinically important difference (MCID) of 2 among patients with CLBP [41].

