#### Low back pain-related disability

The Brazilian Portuguese version of the Oswestry Disability Index (ODI) [27] consists of 10 items, each of which has six response options. The total score will be calculated by summing up all the points, with the largest possible sum being 50. This sum will be transformed into a percentage (0 to 100). ODI showed responsiveness to change for patients with CLBP, with MCID of 10–12 points [41].

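### The sample-size paragraph gives an effect size of f = 0.27 that matches neither outcome assumption and does not lead to 152; the ODI assumption does, but only at an unadjusted alpha of 5%

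*Protocol article*

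**What the plan says.** All the sample-size inputs stand in one paragraph of the Protocol article, under Statistical analysis.

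- **Outcome assumptions**, one for each primary outcome: "an improvement of at least 1-point on the NPRS (SD=1) and a mean difference of at least 5 points for the ODI score (SD=10").
- **Specifications:** "The following specifications were considered: α=5%, 80% statistical power, effect size of 0.27 for" an F-test, followed by 15% attrition at follow-up.
- **Result**, attributed to G*Power: "The final sample size will be comprised of 152 patients (76 per group").

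The paragraph does not say how 0.27 was obtained. It gives no correlation, number of repeated measurements or covariate adjustment that would connect 0.27 to the two outcomes. Later in the same paragraph the p-values for the multiple primary outcomes are to be Bonferroni-adjusted, but that correction is not among the sample-size specifications, which give alpha as 5%.

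**The concern.** A reader who tries to reproduce the calculation meets two mismatches. The effect size cannot be derived from either outcome assumption printed just before it, and entering it with the stated alpha, power and attrition gives a total other than 152. One printed input therefore contradicts both the other inputs and the output.

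What is at stake is the power claim. With two primary outcomes and a planned multiplicity correction, the reader needs to know which outcome set the sample size and at what significance level the 80% applies. The paragraph does not say, and the one number that should link assumptions to sample size points elsewhere.

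**Working it through.** **Inputs**, all from the Statistical analysis section: alpha 5%, power 80%, f = 0.27, NPRS difference 1 with SD 1, ODI difference 5 with SD 10, attrition 15%, two equal arms. Sidedness is not stated; an F-test with one numerator degree of freedom equals a two-sided t-test.

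**Formulas.** Standardised difference d = difference / SD; for two equal groups f = d / 2. Power is the upper tail of a noncentral F with 1 and N − 2 degrees of freedom and noncentrality f² × N. Patients randomised per arm = evaluable per arm / (1 − 0.15), rounded up.

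**Step 1: reproduce 152.** ODI: d = 5/10 = 0.50, f = 0.25. At alpha 5%, 64 per arm (128 in total) gives 80.1% power. 64 / 0.85 = 75.3, so 76 per arm and 152 in total. This matches the stated figure exactly.

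**Step 2: compare 0.27 with the outcome assumptions.**

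| Source | d | f |
|---|---|---|
| NPRS, 1 point, SD 1 | 1.00 | 0.50 |
| ODI, 5 points, SD 10 | 0.50 | 0.25 |
| Stated effect size | 0.54 | 0.27 |

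**Step 3: sample size from each f at alpha 5%, 80% power, 15% attrition.**

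| f | Evaluable per arm (total) | Randomised per arm (total) |
|---|---|---|
| 0.50 | 17 (34) | 20 (40) |
| 0.27 | 55 (110) | 55 / 0.85 = 64.7, so 65 (130) |
| 0.25 | 64 (128) | 76 (152) |

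The gap between 0.27 and the stated total is 152 − 130 = 22 patients, or 22/130 = 17%.

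**Step 4: can unstated inputs take 0.27 to 152?**

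- At the Bonferroni level, 0.05 / 2 = 0.025, the exact F-test needs 67 per arm (134). Dividing by 0.85 gives 78.8, so 79 per arm and 158 in total. Inflating by 1.15 instead gives 134 × 1.15 = 154.1. A normal approximation (66 per arm, 132) times 1.15 gives 151.8, so 152.
- A repeated-measures between-group F-test with two time points, an assumed correlation of 0.9 and alpha 0.025 needs 128, which gives 152 at 76 per arm.
- Baseline adjustment would raise the ODI's 0.25 to 0.27 if the correlation r satisfied 0.25 / √(1 − r²) = 0.27, so r is about 0.38. At alpha 5% that still leads to 130.

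The first two routes need an alpha that differs from the stated 5%. The repeated-measures and baseline-adjusted routes need a correlation that the article does not give.

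**Step 5: power with 128 completers at both levels.**

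| Assumption | alpha 0.05 | alpha 0.025 |
|---|---|---|
| ODI, f = 0.25 | 80.1% | 71.2% |
| Stated f = 0.27 | 85.8% | 78.3% |
| NPRS, f = 0.50 | above 99.9% | above 99.9% |

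**The case against.** The strongest reply is that the enrolment target is sound: 152 follows exactly from the ODI assumption, and had 0.27 truly governed, the trial would be larger than required. On this view one misprinted parameter stands beside a reproducible total, and no enrolment or analysis decision turns on it. Most of this stands. It limits the point to a correction of the stated justification, but it does not make 0.27 consistent with anything printed around it.

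A second reply is that the article says only that an F-test was used, so 0.27 may come from a more elaborate calculation. That is possible, as step 4 shows, and it is why the sponsor should be asked before 0.25 is printed. It does not rescue the text, because each such route needs an input that the article omits or states differently.

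A third reply concerns Bonferroni. If success on either primary outcome suffices, the stated NPRS assumption alone puts the chance of at least one significant result above 99.9%. That is correct, but it does not give the ODI comparison 80% power at its adjusted level.

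A reader might also infer two stronger criticisms that the article does not support.

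- **Targets below the MCIDs.** The outcome sections describe the NPRS "with a minimum clinically important difference (MCID) of 2 among patients with CLBP" and the ODI "with MCID of 10–12 points", while the calculation uses 1 and 5 points. The article never calls 1 or 5 points an MCID. Powering for a smaller difference gives more power for the larger one, and 95% confidence intervals are already planned. This is not an error.
- **An NPRS SD that is too small.** If 0.27 had come from the 1-point target, the SD would be 1/0.54 = 1.85. That is a back-calculation from a supposition. No NPRS SD other than 1 appears in the article, and NPRS did not set the sample size.

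**Conclusion.** The point holds as an inconsistency in the stated justification. The effect size of 0.27 agrees with neither outcome assumption (0.50 and 0.25), and with the stated alpha, power and attrition it gives 130 randomised patients, not 152. The total of 152 is exactly what the ODI assumption gives at an unadjusted 5%. At the Bonferroni level of 0.025, the same 128 completers give about 71% power for the ODI target.

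It would be wrong to conclude that 152 is unsupported, or that the trial is too small at the alpha it states. Nor do the documents show that 0.25 was in fact the value entered; the exact match makes that a strong inference and no more.

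The figures assume a two-group, two-sided comparison at a single time point, equal arms, attrition handled as n / 0.85, and Bonferroni as an equal split over two outcomes.

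**What to change.** 1. Check the G*Power record for the effect size, test family, alpha and attrition step actually used.
2. Then either state how 0.27 was derived, with every input needed to reach 152, or replace it with f = 0.25 and name the ODI as the limiting outcome (5 points, SD 10, 64 evaluable and 76 randomised per arm at 15% attrition).
3. State the alpha used in the calculation, and restate power at the Bonferroni level. If 0.25 is confirmed, with 128 completers: ODI about 80% at 0.05 and about 71% at 0.025; NPRS above 99.9% at either level with the stated SD of 1.

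Replacing 0.27 with 0.25 without step 3 would leave an 80% claim that does not describe the planned adjusted test. No change to the NPRS SD or to the MCID wording is required.

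The cost is a text correction with no change in enrolment. The downside is a less favourable stated power for the ODI.

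### The sample size uses an undivided alpha of 5%, but Bonferroni tests each primary outcome at 2.5%: power for ODI is about 71%, not 80%; Holm would restore it on the plan's own assumptions

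*Protocol article*

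**What the plan says.** Outcome measures names two primary outcomes: "The primary outcomes in the current study will be pain intensity" and low back pain-related disability, both collected post-intervention.

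Statistical analysis bases the sample size on both: "Two primary outcome variables were considered for the calculation of sample size". The inputs are 1 point on the NPRS with SD 1, and "a mean difference of at least 5 points for the ODI score (SD=10"). It continues: "The following specifications were considered: α=5%, 80% statistical power", with an "effect size of 0.27 for" an F-test and 15% follow-up attrition. The result is 152 patients, 76 per group.

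Later in the same paragraph, after a 0.05 significance level is set, comes the multiplicity rule: "The Bonferroni correction will be used to adjust the" p-values of the multiple primary outcomes. On estimation the section says: "The between-group differences (effects of treatment) and their respective 95% CIs will be calculated by constructing linear mixed models".

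Nowhere does the article say that the 5% in the sample size calculation was divided between the outcomes, and it names no stepwise procedure.

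**The concern.** Bonferroni over two outcomes rejects each one only if its unadjusted p-value is at most 0.05/2 = 0.025. A sample size computed at 0.05 therefore describes a more lenient test than the one that will be run. NPRS has power to spare under the stated assumption; ODI, which drives the sample size, has none. A non-significant ODI result would be read as coming from a test with a 20% type II error when, on the plan's own inputs, that error is about 29%.

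A smaller mismatch follows. A 95% confidence interval corresponds to a 0.05 test. If a primary outcome has an unadjusted p-value between 0.025 and 0.05, its interval excludes zero while its Bonferroni-adjusted p-value is not significant, and the plan does not say which governs the conclusion.

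**Working it through.** **Inputs** (Statistical analysis, protocol article): ODI difference 5, SD 10; NPRS difference 1, SD 1; alpha 5%; power 80%; attrition 15%; 76 per arm. The test is taken as two-sided because the sizing uses an F-test.

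**Standardised effects.** d = difference / SD. ODI: 5/10 = 0.50. NPRS: 1/1 = 1.00. For two equal groups f = d/2, giving 0.25 and 0.50.

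**Reproducing 152.** Two-sample t-test with noncentral t, df = 2n − 2 and noncentrality d·√(n/2). For d = 0.50 at two-sided 0.05, 80% power first occurs at n = 64 per arm (63 gives 79.5%, 64 gives 80.1%). Then 64/(1 − 0.15) = 75.3, rounded up to 76 per arm, or 152 in total. This is the plan's figure exactly, obtained with an undivided alpha.

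**Same design at the Bonferroni level.** With n = 64, df = 126 and noncentrality 0.50·√32 = 2.83, the critical value rises from 1.979 (alpha 0.05) to 2.269 (alpha 0.025).

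| Outcome, 64 per arm | alpha 0.05 | alpha 0.025 |
|---|---|---|
| ODI, d = 0.50 | 80.1% | 71.2% |
| NPRS, d = 1.00 | 99.99% | 99.96% |

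**Cost of keeping both Bonferroni and 80%.** At 0.025, d = 0.50 needs 78 per arm (77 gives 79.8%, 78 gives 80.4%). 78/0.85 = 91.8, so 92 per arm and 184 in total, 32 more than planned.

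**Holm.** The smaller p-value is compared with 0.025; if it is rejected, the other is compared with 0.05. Under the plan's NPRS assumption pain is rejected at 0.025 with probability 99.96%, so ODI is almost always tested at 0.05. Simulated pairs of correlated t statistics give 80.2% for ODI. How far this depends on the true pain effect (ODI d = 0.50, 64 per arm, correlation 0 and 0.5):

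| NPRS d | ODI power, Bonferroni | ODI power, Holm |
|---|---|---|
| 1.00 (plan) | 71% | 80% |
| 0.75 | 71% | 80% |
| 0.50 (SD 2, assumed) | 71% | 77–78% |
| 0.25 | 71% | 72–73% |
| 0 | 71% | 71% |

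With NPRS d = 0.50 and a correlation of 0.3 to 0.5, both outcomes are significant in 66–68% of trials under Holm and 54–57% under Bonferroni.

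**Sensitivity of the ODI figure at 0.025**
- 70 evaluable per arm: 75.5%. All 76: 79.2%.
- 24% attrition: 76 × 0.76 = 57.8, so 57–58 per arm, giving 65–66%. The Discussion reports follow-up losses above 24% in earlier CFT trials.
- f = 0.27 (d = 0.54), 64 per arm: 78.3%.
- Baseline adjustment, dividing d by √(1 − r²) and treating SD 10 as unadjusted: 75.6% for r = 0.3, 79.2% for r = 0.4, 83.9% for r = 0.5. These r values are assumptions; the article gives none.

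**The case against.** **The planned model adjusts for baseline, so 71% is not its exact power either.** This is the strongest point and it partly stands. With a baseline–outcome correlation a little above 0.4 the model recovers 80% at 0.025. But the article gives no correlation, does not say whether SD 10 is already adjusted, and reaches 152 without using one. The stated 80% therefore does not rest on it.

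**The stated effect size is f = 0.27, not 0.25.** True, but 0.27 matches neither outcome's stated difference and SD, and at alpha 5% it gives 55 per arm, or 130 in total after attrition. A silently divided alpha does not explain 152 either: f = 0.27 at 0.025 needs 67 per arm, or 158 in total. Multiplying by 1.15 instead of dividing by 0.85 comes closer (134 × 1.15 = 154), but would mean reading the stated 5% as familywise. Even at f = 0.27, power at 0.025 with 64 per arm stays below 80%. The mismatch should be reconciled separately.

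**Loss by the post-intervention visit may be below 15%.** It may, since that visit comes after only 5 to 7 weekly sessions. Complete data on all 76 per arm would still give 79.2%. For the same reason the 24% scenario is only a lower illustration.

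**Bonferroni is valid, and at least one rejection is nearly certain.** Both are true. Type I error is controlled and nothing is biased. The near-certain rejection is for pain, however, and rests on an SD of 1; the power problem concerns disability.

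**Holm does not guarantee 80% and does not settle the interval question.** Correct. It restores 80% only if pain is rejected, and intervals that match Holm are less simple. If both p-values lie between 0.025 and 0.05, both ordinary 95% intervals exclude zero and Holm rejects neither. Even so, Holm never does worse than Bonferroni.

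**Conclusion.** The concern holds. The sample size and the multiplicity rule use different alphas, and the stated 80% power is not that of the planned test. On the protocol's own ODI inputs, two-sided, with 64 evaluable per arm and no credit for baseline adjustment, power for ODI is 71.2%, a shortfall of about 9 percentage points. More complete data or the larger f narrow the gap to 78–79% without closing it. Only a baseline correlation above about 0.4, which the sizing does not use, would close it at the Bonferroni level. Power for pain is unaffected under the stated SD of 1. The confidence-interval mismatch is real but secondary.

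**What to change.** 1. Replace Bonferroni with Holm for the two primary outcomes: the smaller p-value against 0.025 and, if it is rejected, the other against 0.05.
2. Restate the power beside the sample size: about 80% for ODI under Holm, conditional on the stated NPRS effect (about 77% if the NPRS SD is 2, near 71% if pain shows no effect). If Bonferroni is kept, state about 71%.
3. If Bonferroni is kept, report 97.5% confidence intervals for the primary outcomes. Under Holm, say that the 95% intervals are unadjusted and that the adjusted p-values decide significance.
4. If credit for baseline adjustment is wanted, state the assumed correlation and its source.

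**Cost.** No extra patients, and familywise error stays at 5%. The text change is small, but recruitment began in May 2021, so the new decision rule should be a dated amendment made before anyone sees outcome data by arm. Keeping Bonferroni costs a less favourable stated power; keeping it together with 80% power would cost 32 more patients.
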